### Interim analyses {21b}

Interim analyses of primary and secondary outcomes will be conducted at the mid-way point of the RCT, when approximately 90 participants have completed the post-intervention questionnaires (T2). Minor changes in intervention delivery (e.g., offering optional in-person group therapy, updating DBT homework, changing video production) may be made based on results from interim analyses. Any changes to intervention delivery will be documented in a protocol deviation document.

### Methods for additional analyses (e.g., subgroup analyses) {20b}

Subgroup analyses may be conducted based on attendance at telehealth sessions to evaluate whether those who do not attend sessions regularly achieve the same benefit as those who do. Additional subgroup analyses, based on emerging research questions of interest, may be conducted as well.

### Methods in analysis to handle protocol non-adherence and any statistical methods to handle missing data {20c}

All analyses will employ intent-to-treat (ITT) methods, meaning that all participants randomized, whether they receive their allocated intervention or withdrew from the study, will be included [72]. Additionally, analyses using only data from participants who completed the intervention will be conducted for comparison purposes. In these analyses, missing data will be handled using maximum likelihood, which estimates values based on all available data and thus produces unbiased model parameters and standard errors.

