### Outcomes {12}

#### Primary outcomes (the specific measures utilized are described below in data collection and management)

The primary outcome of this study is mean change in depressive symptoms in mothers from pre- to post-intervention as measured by a self-report questionnaire [39]. Another primary outcome of this study is mean change in child behavioral problems from pre- to post-intervention, measured by parent-report questionnaire [47].

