#### Plans to promote participant retention and complete follow-up {18b}

Participants will receive weekly email or SMS text reminders containing information for telehealth sessions. Participants will receive an additional $10 CAD if they complete the post-intervention and follow-up surveys in a timely manner.

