## Statistical methods

### Statistical methods for primary and secondary outcomes {20a}

Analyses for primary and secondary outcome variables, as well as exploratory outcome variables, will compare the changes over time between (a) the BRIDGE vs SAU groups and (b) BRIDGE vs DBT-only groups, each at *a* = 0.025 (combined type I error rate to 0.05). Linear models accounting for pre-intervention scores will be used as the primary analysis method. The persistence of effects at the 6-month follow-up will be examined using time-by-intervention interactions in a linear mixed-effects model, accounting for within-subject serial correlations and between-subject effects of the intervention and covariates. Standardized effect sizes for linear mixed models will be derived based on recommendations for linear mixed models [70, 71]. Standardized effect sizes of 0.20, 0.50, and 0.80 will be used to interpret small, medium, and large effects, respectively [70]. The research team will also investigate if there is baseline moderation by symptom severity to examine whether the BRIDGE intervention is more effective than the DBT-only or SAU interventions for participants who have higher symptom levels at pre-intervention.

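### As named, the primary T2 model gives no weight to a mother without a T2 score, and maximum likelihood is not unbiased merely because it uses all available data

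*Protocol article*

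**What the plan says.** The protocol article bears on this in three places.

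- **Outcomes {12}.** The first primary outcome is "mean change in depressive symptoms in mothers from pre- to post-intervention as measured by a self-report questionnaire". The second, child behaviour problems, is defined over the same two time points. The primary contrasts are therefore at T2.
- **Statistical methods for primary and secondary outcomes {20a}.** "Linear models accounting for pre-intervention scores will be used as the primary analysis method". A different model is then named for a different question: "The persistence of effects at the 6-month follow-up will be examined using time-by-intervention interactions in a linear mixed-effects model".
- **Non-adherence and missing data {20c}.** Under intention to treat, "all participants randomized, whether they receive their allocated intervention or withdrew from the study, will be included". The section adds that "analyses using only data from participants who completed the intervention will be conducted for comparison purposes". Its last sentence refers back to the analyses just mentioned and says that missing data in them will be handled by "maximum likelihood, which estimates values based on all available data and thus produces unbiased model parameters and standard errors".

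The article attaches no condition to that last statement and gives no expected loss at T2.

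**The concern.** There are two difficulties.

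First, section {20a} names a model with one post-intervention score as outcome and the pre-intervention score as covariate, whereas {20c} promises that all randomised mothers are included by way of maximum likelihood. For a model of that form, maximum likelihood does not bring in a mother whose outcome is missing. The model that could use her T3 score is assigned to another question.

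Second, {20c} derives unbiasedness from the use of all available data. That does not follow. Likelihood estimates are valid, in large samples, if data are missing at random given what is in the model and if the model is correctly specified. Here that condition cannot be taken for granted: participants are not blinded {17a}, both primary outcomes are reported by the mother {18a}, and the rules on ending programme participation ({11b}, {11c}) concern programmes that the services-as-usual (SAU) arm does not receive.

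At stake is whether the primary estimate could be reported as an unbiased analysis of all randomised mothers when neither description is assured.

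**Working it through.** **1. The plan's own figure.** Sample size {14} gives 75% power for BRIDGE versus DBT-only on child symptoms, with 60 per arm and d = 0.54; {20a} sets 0.025 per comparison. Noncentrality = d × √(n/2) = 0.54 × √30 = 2.96, with 118 degrees of freedom. Taken as two-sided, this gives 75.3% (76.3% by the normal approximation). The figure reproduces, and it assumes a T2 score from all 60 mothers per arm.

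**2. How many mothers.** The background section {6a} reports pilot retention of 86% and 92.3%. Used as a proxy for T2 return:

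- 180 × (1 − 0.923) = 13.9, about 14 mothers
- 180 × (1 − 0.86) = 25.2, about 25 mothers

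With only observed T2 scores, the calculation in step 1 gives 71.1% at 55 per arm (60 × 0.923 = 55.4) and 68.4% at 52 per arm (60 × 0.86 = 51.6). These are illustrations, because the pilot figures describe retention in BRIDGE, not questionnaire return in three arms.

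**3. What likelihood does with T1 and T2 only.** The joint density factors as f(T1, T2 | arm) = f(T1 | arm) × f(T2 | T1, arm). The treatment effect sits in the second factor, and a mother with T1 alone contributes only to the first. A simulation confirmed this: the largest difference between the T1-T2 likelihood estimate and complete-case analysis of covariance (ANCOVA) in any trial was below 1e-8. When T3 was added, single-trial estimates moved by up to about 0.1 SD, because mothers with T3 but no T2 then contributed.

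**4. Is maximum likelihood unbiased?** The same simulation used 400 trials per mechanism, 60 per arm and a true effect of −0.54 SD. Assumed correlations were 0.6 (T1-T2), 0.5 (T1-T3) and 0.7 (T2-T3). Of the mothers without T2, 70% were assumed to lack T3 as well. The Monte Carlo standard error is about 0.008.

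| Dropout at T2 | Mean missing | Complete-case ANCOVA | Likelihood, T1-T2 | Likelihood, T1-T3 |
|---|---|---|---|---|
| Completely at random | 14.0% | −0.532 | −0.532 | −0.532 |
| Depends on T1 (missing at random) | 14.4% | −0.542 | −0.542 | −0.542 |
| Depends on the unseen T2 score in the treated arm, flat 14% in control | 15.2% | −0.652 | −0.652 | −0.640 |

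In the last row the effect is too large by 0.652 − 0.54 = 0.112 SD with T1-T2 and 0.640 − 0.54 = 0.100 SD with T1-T3. All available data are used in both, and both are biased.

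**5. Direction.** Suppose mothers without T2 are worse by a shift s than observed mothers in the same arm with the same T1 score. The BRIDGE benefit over SAU is then overstated by (missing share in BRIDGE − missing share in SAU) × s. For assumed shifts of 3 to 5 PHQ-9 points:

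- 14% missing in BRIDGE, 8% in SAU: 0.06 × 3 = 0.18 to 0.06 × 5 = 0.30 points overstated
- 8% in BRIDGE, 14% in SAU: 0.18 to 0.30 points understated
- equal shares and equal shifts: no bias

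The documents do not say which case applies.

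**The case against.** The strongest reply is that the article excludes nobody. Section {20c} includes everyone randomised and names maximum likelihood, and {20a} speaks of linear models without restricting them to observed T2 scores. The exact likelihood model is a detail that a condensed article may leave to the full plan. The repair also gains little: under missingness at random there was no material bias to remove, and under informative dropout adding T3 removed only 0.652 − 0.640 = 0.012 SD.

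Much of this stands, and it rules out three stronger readings.

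- A reader might infer that the trial will drop every mother without T2 and so not analyse the intention-to-treat set. The article does not say so. It is a consequence of the model as named, and it would not hold for a joint model that uses T3.
- A reader might infer that maximum likelihood applies only to the completer analyses, leaving the intention-to-treat analyses with no method. The section opens with all analyses, so the back-reference can fairly cover both. The wording is ambiguous, not wrong.
- A reader might infer a bias in favour of BRIDGE from "Participants will receive weekly email or SMS text reminders containing information for telehealth sessions", since SAU has no such sessions. The same section pays $10 CAD for timely post-intervention and follow-up surveys, and Recruitment {15} pays $50 CAD for the post-program questionnaires; neither is limited by arm. If SAU did lose more mothers, with equal shifts, step 5 shows that the benefit would be understated.

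Two things survive. Section {20a} sets the mixed model apart from the primary method, so the natural reading of the primary method does not include T3. And the sentence on unbiasedness is untrue as written, whatever a fuller plan adds.

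**Conclusion.** The point holds in a limited form. As named, the primary model gives no weight to a mother without T2, even if she has T3, which does not sit with the promise to include all randomised mothers. The reason given for unbiasedness is incorrect.

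The number affected is about 14 to 25 of 180 if T2 loss matches pilot dropout, which is an assumption. No bias of known size or sign can be claimed. The 0.10-0.11 SD in the simulation rests on assumed correlations and one assumed dropout mechanism, and the PHQ-9 figures rest on assumed shifts and loss rates. This should be corrected because it concerns the primary estimate and the change is small, not because the trial's result is shown to be wrong.

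**What to change.** - In {20a}, estimate the primary T2 contrasts from the likelihood-based mixed model already planned, with T1, T2 and T3 as outcomes, baseline means constrained equal across arms and an unstructured covariance. T1 is completed before randomisation, so all 180 mothers enter. Those with T3 but no T2 then inform the T2 contrast; those with T1 only still do not.
- In {20c}, replace the claim of unbiasedness with: valid under missing at random and a correctly specified model.
- In {20c}, state that this handling applies to the intention-to-treat analyses as well as the completer analyses.

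The cost is wording and the re-use of a planned model. The change should be dated and made before outcomes are compared by arm, including at the interim analysis {21b}.

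Because the T1-T3 model is still biased when dropout depends on the unseen T2 score, a sensitivity analysis that worsens missing T2 scores by a range of amounts, separately by arm, is a cheap addition. Its downside is one more analysis to run and report. Its absence from the article is not itself an error.

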### Plans to give access to the full protocol, participant level-data and statistical code {31c}

As principal investigator, [name] will be primarily responsible for data management. Data analysis will occur independently. Data will not be released to any third party (including the funder) before the trial is completed. De-identified participant data will be made publicly available after the initial publication of results on an open-access platform and will also be available upon request from the primary investigator. Statistical code will also be available upon request following the publication of the results.

#### Composition of the data monitoring committee, its role and reporting structure {21a}

The current trial does not have a formal data monitoring committee. Instead, research assistants will meet weekly with the principal investigator, [name], to review ongoing trial activities. The clinical team will meet weekly during the intervention to discuss any questions or concerns that arise during telehealth sessions.

#### Adverse event reporting and harms {22}

No adverse events were reported in the pilot studies of the BRIDGE intervention. A risk management protocol exists for mental health crises or child maltreatment concerns. If a participant in the BRIDGE or DBT interventions reports increasing psychological distress throughout the intervention, a clinician will meet with them individually and may connect them to more intensive mental health services if necessary. The primary investigator will be informed of any participant crises or concerns and respond appropriately. Any adverse events will be reported to the University of Manitoba Research Ethics Board and our research team will comply with their instructions.

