##### SAU

Participants in the SAU condition will receive a list of local mental health and parenting resources, curated by our research team, and can access any intervention or resource they would like throughout the duration of the program.

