#### Strategies to improve adherence to interventions {11c}

To encourage engagement with the program, participants will be required to confirm their availability to attend weekly virtual group therapy sessions. Before starting the BRIDGE or DBT intervention, participants will attend a Zoom orientation meeting with a clinical coach. The purpose of the orientation meeting is to welcome participants to the program, explain the program components, review DBT assumptions and guidelines, assess safety and risky behaviors (e.g., suicidal or self-harm behavior, substance use), and answer questions. As some topics are not discussed in group given the potential to negatively affect other group members, the orientation meeting serves to assess the risk for drop-out, validate the importance of these safety concerns, and inform participants on how to reach out to facilitators individually on these topics (e.g., pre- or post-group check-ins, individual meetings outside of group time). As standard practice, participants in the BRIDGE and DBT conditions will be sent an email or SMS text reminder once per week for that week’s group and content. Should participants not present to their respective groups, a clinical coach will contact them at the 5-min mark to provide the Zoom link and invitation to join. Additional follow-up will occur for participants who miss the session and are non-responsive to the reminder. Contact will occur through multiple methods and with the use of validation and encouragement to support participants returning to the group. Participants will be informed that missing four sessions without being responsive to communication and efforts to return to the group will result in discontinued treatment.

To ensure adherence to the DBT Skills group protocol and assumptions during weekly therapy sessions, our team created a clinician-reported adherence measure. The measure was adapted from Harned and colleagues [44] for group therapy, with the integration of relevant resources [45, 46]. The measure was reviewed by experts in DBT (and co-authors on the current study) and refined. The resulting measure consists of 30 items rated as adherent, not adherent, or not applicable. Clinicians in both the BRIDGE and DBT groups will complete the adherence measure after each therapy session.

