#### Relevant concomitant care permitted or prohibited during the trial {11d}

Participants will remain eligible for inclusion in the study if they receive concomitant care for mental health or parenting concerns; this will be documented and controlled for in the analysis as appropriate. Participants who are identified as having mental health concerns beyond depressive symptoms will be given access to a resource list of mental health and parenting supports and services which they may access during the program. Participants may continue with or begin additional clinical care (e.g., individual psychotherapy, psychiatric medications) throughout their study involvement. Additionally, participants who present with elevated suicidality or substance use either during the screening process or throughout the intervention will be offered appropriate care (e.g., monthly individual meetings with a clinician) or referred for additional clinical care.

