### Participant timeline {13}

Week 0 (T1): Eligible consenting participants will receive a notice of enrollment via email. Exploratory outcomes will be assessed at this time point via opt-in virtual Zoom assessments. Participants will complete a 45-min baseline questionnaire, including primary, secondary, and exploratory outcomes. The T1 timepoint will be approximately 8 weeks prior to the start of the intervention.

Week 8: Participants randomized to either intervention condition will be sent an email regarding website login information. Participants will attend a clinical orientation meeting with clinical coaches.

Weeks 9–24: Participants in the BRIDGE condition will watch DBT and parenting skills training videos and complete the accompanying worksheets weekly. Participants in this condition will also complete brief weekly symptom tracking questionnaires and attend weekly virtual group therapy sessions.

Participants in the DBT condition will attend weekly virtual group therapy sessions and will complete educational worksheets. They will also complete brief weekly symptom tracking questionnaires.

Week 25 (T2): Participants will complete questionnaires assessing primary, secondary, and exploratory outcomes. Additional exploratory outcomes will be assessed via virtual Zoom assessment and co-parent questionnaire completion.

Week 25 + 6 months (follow-up): Six months post-intervention, participants will complete a 45-min follow-up questionnaire to assess prolonged changes in primary and secondary outcomes, as well as exploratory outcomes related to family relationships, maternal mental health symptoms, recent stressful experiences, and health and social services usage (Table 1).

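### Monitoring for worsening between visits is described only for BRIDGE and DBT, so spontaneously recorded adverse events are not comparable with services as usual

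*Protocol article*

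**What the plan says.** Under Adverse event reporting and harms {22} of the protocol article, the response to rising distress names two arms: "If a participant in the BRIDGE or DBT interventions reports increasing psychological distress throughout the intervention, a clinician will meet with them individually". The same section has two sentences with no arm limit: "The primary investigator will be informed of any participant crises or concerns and respond appropriately", and "Any adverse events will be reported to the University of Manitoba Research Ethics Board and our research team will comply with their instructions". It also mentions a risk management protocol for crises and child maltreatment concerns, which is not reproduced. The section describes where events are sent, but no method of asking about them that is common to all arms.

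The other routes by which worsening could surface between visits are these:

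- Strategies to improve adherence {11c}: "Before starting the BRIDGE or DBT intervention, participants will attend a Zoom orientation meeting with a clinical coach". That meeting includes an assessment of safety and risky behaviour.
- Participant timeline {13}, for BRIDGE: "Participants in this condition will also complete brief weekly symptom tracking questionnaires and attend weekly virtual group therapy sessions". For DBT, which also has weekly sessions: "They will also complete brief weekly symptom tracking questionnaires".
- Composition of the data monitoring committee {21a}: there is no formal committee. The clinical team meets weekly about matters arising in telehealth sessions.

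For the control arm, the section SAU says: "Participants in the SAU condition will receive a list of local mental health and parenting resources, curated by our research team". No contact with these mothers is described from then until the T2 questionnaire.

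The section on concomitant care {11d} is worded without an arm: "participants who present with elevated suicidality or substance use either during the screening process or throughout the intervention will be offered appropriate care".

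**The concern.** All mothers enter with a PHQ-9 score of 10 or more, and the article itself treats suicidality, self-harm, substance use and child maltreatment as risks to be managed. If events are recorded when someone happens to hear of them, the count in each arm depends on how often staff speak to the mothers as well as on how often events occur. Here contact differs sharply by design between the active arms and SAU. A tally by arm, in a report to the ethics board or in the results paper, would then tend to show more events under BRIDGE and DBT even if the true rates were equal. It would also tend to understate events among SAU mothers. Nothing described would correct this during the trial: there is no formal data monitoring committee, and the interim analysis in {21b} covers primary and secondary outcomes only.

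**Working it through.** The plan gives no figure to reproduce on this point. The check has three steps.

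**1. Routes of detection between T1 and T2, by arm** (sections {11a}, {11c}, {13}, {21a}, {22} and SAU)

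| Route | BRIDGE | DBT | SAU |
|---|---|---|---|
| Orientation meeting with safety assessment (week 8) | 1 | 1 | 0 |
| Weekly group sessions (weeks 9–24) | 16 | 16 | 0 |
| Clinician meeting for rising distress | yes | yes | not described |
| Weekly team discussion of session concerns | yes | yes | no sessions |
| Weekly mood surveys | 16 | 16 | 0 |

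Scheduled contacts with clinical staff: 1 + 16 = 17 in each active arm against 0 in SAU. The surveys would raise the total to 17 + 16 = 33. They are described as returning scores to the mother, however, and the article does not say that staff review them, so 17 is the safer count. T1 is week 0 and T2 is week 25. The difference in contact falls in weeks 8 to 24; before week 8 no clinical contact after T1 is described for any arm.

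**2. What is measured alike in all arms** (Trial design {8}, Participant timeline {13}, Plans for assessment {18a})

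The PHQ-9, other maternal symptom scales and the service-use scale are collected at T1, T2 and T3 in every arm. Symptom change to T2 and T3 is therefore ascertained equally. These measures do not replace event items, for two reasons:

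- The service-use scale looks back 3 months, about 13 weeks. At T2 that leaves about 25 − 13 = 12 weeks since T1 uncovered; at T3 it covers about half of the 6 months since T2.
- As described, it counts contacts with services such as hospital visits. It is not stated to capture suicide attempts or self-harm.

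**3. Illustration of the bias** (the event rates and detection probabilities are assumptions; only the arm size of 60 is from the article)

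Expected recorded events = 60 × true rate × detection probability. With the same true rate in both arms, the apparent ratio is simply detection in the active arm divided by detection in SAU. At a true rate of 5% there are 60 × 0.05 = 3 true events per arm:

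| Detection, active v SAU | Recorded, active v SAU | Apparent ratio |
|---|---|---|
| 70% v 50% | 2.1 v 1.5 | 1.4 |
| 90% v 50% | 2.7 v 1.5 | 1.8 |
| 90% v 30% | 2.7 v 0.9 | 3.0 |
| 90% v 20% | 2.7 v 0.6 | 4.5 |

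The ratios do not depend on the true rate, but the counts do. At 20% the second and last rows become 10.8 v 6.0 and 10.8 v 2.4. At 5% the difference is 0.6 to 2.1 events per arm. The direction holds whenever contact raises detection; the size is not known.

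**The case against.** A reader might infer more than the article supports, in four ways.

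- *That adverse events are reported only in the active arms.* Not so. The sentences on informing the primary investigator and reporting to the ethics board have no arm limit. What differs is the chance that an event is heard of.
- *That harms cannot be compared across arms, or that deterioration in SAU stays unseen.* Not so. Depressive symptoms are a primary outcome measured identically in all arms at T1, T2 and T3, so worsening still present at those points is visible. BRIDGE and DBT have similar contact, so events can be compared between those two with little difficulty.
- *That the sections on concomitant care {11d} and on harms {22} contradict each other.* They have different triggers, elevated suicidality or substance use in one and rising distress in the other. A general rule and a narrower one can coexist. They are unclear about SAU rather than contradictory.
- *That the active programmes would show a given multiple of SAU events.* The detection probabilities are assumed, and the counts may differ by only one or two events.

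Three further objections carry some weight. The risk management protocol and the schedule in Table 1 are not shown, and either may cover SAU mothers. The article plans no arm-by-arm analysis of adverse events. And little study contact is inherent in a services-as-usual arm.

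These limit the point without removing it. The distress response is explicitly confined to two arms in the text at hand. Any later report that gives events by arm would inherit the unequal ascertainment. The remedy needs no extra contact with SAU mothers between visits.

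**Conclusion.** The point stands as one about ascertainment. Staff contact through which worsening could surface between T1 and T2 is described for BRIDGE and DBT (17 scheduled contacts per mother) and not for SAU (none). Spontaneously recorded adverse events are therefore not comparable between the active arms and SAU, and the bias would tend to run against the programmes. Its size cannot be derived from the document; the ratios of 1.4 to 4.5 rest wholly on assumed detection probabilities. Comparison of symptom scores at T2 and T3 is unaffected, and BRIDGE against DBT is little affected. The conclusion assumes that the risk management protocol and Table 1, neither of them shown, add no equivalent contact or event questions for SAU. This is a worthwhile, low-cost improvement and does not threaten the primary analysis.

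**What to change.** 1. Add the same short set of adverse-event items to the T2 and T3 questionnaires in all three arms, each asked for the period since the last questionnaire: for example suicide attempt, self-harm needing medical attention, and psychiatric emergency visit or admission. The eligibility criteria already use the first two, so similar wording is at hand.
2. State that any comparison of harms with SAU rests on these items, and that events found through sessions or other programme contact are listed separately.
3. Reconcile the sections on concomitant care {11d} and on harms {22} so that it is clear whether the risk response applies to SAU mothers and to answers given at T2 and T3. Which clinical rule applies is for the investigators and the ethics board.

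Cost: a few REDCap items in questionnaires already sent to everyone, an ethics amendment, and about a minute of each mother's time. The items rely on recall over about 25 weeks to T2 and 6 months to T3, and they miss mothers who do not return the questionnaire. Coverage will be incomplete: the article reports 78 mothers already randomised, with first-round T2 assessments under way. The remaining 180 − 78 = 102 could be covered at both T2 and T3, and the first round at T3 if the amendment is prompt. If the reconciled text extends the risk response to SAU, a few mothers there would have study contact, which slightly dilutes that condition.
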